## Abstract

**Introduction:**

Painful diabetic neuropathy (PDN) is a common complication of diabetes that leads to significant co-morbidity. Emerging evidence suggests glycaemic variability may be linked to fluctuations in pain intensity. Hybrid closed loop (HCL) systems reduce glycaemic variability, raising the possibility that they may modify pain intensity. This study aims to evaluate the effects of HCL use on pain intensity in people with PDN.

**Materials and methods:**

PAINLESS is a two-centre, randomised cross-over study, recruiting 49 adults with type 1 diabetes and PDN. Each participant will complete two 12-week intervention periods in a randomised sequence (1:1): one with standard care including continuous glucose monitoring (CGM) and one with HCL using the Tandem t:slim X2 insulin pump with Control-IQ technology. The primary outcome is the change in 7-day average 24-hour pain intensity [rated on a numerical scale from 0-10 (NRS)] from baseline to the end of each 12-week intervention period as measured by daily pain diaries. Secondary outcomes include measures of pain trajectory/durability [responder rates (30% and 50% pain reduction in 7-day NRS), and the AUC for daily NRS scores], functional and quality of life outcomes [Short Form Health Survey (SF-36), and Short Form of the Brief Pain Inventory (BPI-MSF)], mood [Beck Depression Inventory (BDI)], health status [EQ-5D-5L], and global improvement [participant and clinician reported global impression of change]. Exploratory endpoints will harness neurophysiological assessments including Sudoscan, DPN-Check, Vagus and Vibrosense, and sleep and activity data from Withings devices. Statistical analyses will employ an intention-to-treat approach and mixed effect models.

**Timelines:**

24-month trial: 18 months recruitment/follow up, 6 months close-out, analyses and dissemination.

**Registration Details:**

ISRCTN24233750.

## Introduction

Diabetic peripheral neuropathy (DPN) is the most common complication of diabetes [1]. Although DPN can be asymptomatic, up to one-third have painful diabetic neuropathy (PDN) [2]. This is a disabling condition with a profound impact on quality of life, sleep, and mental health [3]. Current pharmacotherapy offers limited efficacy and tolerability [4] with only 54% of patients achieving 50% pain relief on maximal combination therapy [5]. Options for ‘refractory’ neuropathic pain (NeuP) are limited. Opioids carry significant risks and offer no long-term benefit [6], while spinal cord neuromodulation is invasive, costly and unsuitable for many [7]. Other interventions lack robust evidence or availability [4], leaving a major unmet clinical need.

Glycaemic variability (GV), reflecting fluctuations in glucose independent of overall glycaemic exposure, has been linked to fluctuations in pain intensity and has been identified as a potential modifiable therapeutic target [8]. Putative biological mechanisms to suggest the link between glycaemic variability and pathogenesis of diabetic neuropathy have been proposed, primarily via the induction of oxidative stress and systemic inflammatory responses [9]. Specifically, GV has been demonstrated to trigger the NF-kB and PKC pathways, leading to cellular damage that manifests as neuropathy. Continuous glucose monitoring (CGM) now allows precise measurement of GV, including coefficient variation (CV) and standard deviation of glucose (SD) [10]. A meta-analysis of 3,649 people with type 1 diabetes (pwT1D) and type 2 diabetes (T2D) demonstrated a two- to three-fold increased risk of DPN in those with higher GV [11]. Furthermore, GV has been specifically implicated in the development of painful over painless diabetic neuropathy [8,12]. Lower time in range (TIR), was significantly associated with an elevated risk and severity of PDN, independent of other risk factors [8]. However, whether reducing GV can directly modify pain intensity in PDN remains unknown.

Hybrid closed loop (HCL) insulin delivery systems automate basal insulin dosing using CGM data and predictive algorithms [13]. Randomised controlled trials consistently show that HCL improves overall glycaemic control and reduces GV [14–17]. This raises the possibility that HCL could modify pain intensity in PDN by stabilising glucose fluctuations.

The PAINLESS study is a two-centre, randomised cross-over trial designed to test this hypothesis. Adults with type 1 diabetes and PDN will receive 12-weeks of advanced HCL (Tandem t:slim X2 insulin pump with Control-IQ technology (Control-IQ)) and 12 weeks of standard care in randomised order. The primary outcome is the within-participant difference in 7-day average 24-hour pain on an 11-point numerical rating scale (NRS), consistent with IMMPACT recommendations for chronic pain trials [18]. Secondary outcomes include a core outcome set that will examine physical and emotional functioning and overall improvement. Finally, an embedded feasibility evaluation will assess acceptability, safety and operational considerations for future national health service roll-out.

## Materials and methods

### Trial design

Each participant will complete a four-week screening period prior to a 24-week treatment period (Figs 1, 2). During screening, participants will complete daily sleep and pain diaries and wear CGM and an activity tracker. Participants with an average pain NRS ≥ 4 in the last 7 days, will be randomised (1:1 ratio) to begin either standard care with CGM or HCL insulin treatment for the first 12 weeks, followed by the alternative intervention for the second 12 weeks. No washout period is planned between intervention arms.

**Fig 1 pone.0357573.g001:**
[figure not shown]
Participant timeline: Schedule of enrolment, interventions, and assessments in Spirit 2025 Format [19]. The study is a randomised crossover design. Only Schedule A is illustrated. In Schedule B, after randomisation participants start at visit 3B and complete the comparator arm first (up to visit 6B), before switching to HCL start and completing visits 3A-7A. In this case, visit 7A is the study close-out for the participant. HCL – Hybrid Closed Loop.

**Fig 2 pone.0357573.g002:**
[figure not shown]
Flow Diagram of the PAINLESS Study. CGM – Continuous Glucose Monitoring, HCL Hybrid Closed Loop. Created in BioRender. [name] (2026) https://BioRender.com/zh6dz7p.

### Eligibility criteria

The PAINLESS study will recruit adults with type 1 diabetes who have experienced daily neuropathic pain for at least 3 months (Table 1). People with type 2 diabetes are not included as the pathophysiology of PDN differs, with greater influence of metabolic syndrome and dyslipidaemia [20]. Eligibility criteria were designed to exclude confounding conditions and mitigate potential barriers to HCL use. Co-enrolment of participants in observational studies is permitted but co-enrolment in other non-pain studies would require trial management group (TMG) approval.

**Table 1 pone.0357573.t001:** Inclusion and exclusion criteria.

Inclusion criteria
• Age > 18 years.
• Clinical diagnosis of type 1 diabetes for at least 5 years [commenced on insulin treatment within one year of diagnosis].
• Probable neuropathic pain > 3 months confirmed by IASP (NeupSIG) criteria.
• Distal symmetrical polyneuropathy confirmed by the Toronto Clinical Neuropathy Score >5.
• Douleur Neuropathique 4 score >4 at screening visit to confirm NeuP diagnosis.
• HbA1c between 6.5 to 13% (47–118 mmol/mol).
• No change to dose of neuropathic pain medication within the last month.
• 7-day average pain NRS ≥ 4/10 during the final week of the Screening Period.
• Willing and able to comply with the study schedule and be available for the treatment duration.
• Able to give written informed consent.
**Exclusion criteria**
• Non-diabetic neuropathies.
• Predominantly nociceptive, mixed or other more severe pain (unless transient) – to ensure diagnostic specificity, and avoid confounding, as mechanisms and response differ from NeuP.
• Cognitive impairment or consent issues: to ensure ethical consent and valid, reliable self-report pain data.
• Pregnancy/breast feeding or planning pregnancy during the course of the study.
• Visual or hearing impairment, which would impede ability to use technological interventions

IASP – International Association for the Study of Pain; NeupSig – Neuropathic Pain Special Interest Group; NeuP – Neuropathic Pain; NRS – Numerical Rating Scale.

### Study setting and recruitment

To account for anticipated dropout and screen failure rate, the PAINLESS study will enrol approximately 49 participants in the screening period to achieve a randomised sample size of 40 participants in total across two research sites in the United Kingdom – Sheffield Teaching Hospitals National Health Service (NHS) Foundation Trust and University Hospitals of Leicester NHS Trust. The study recruited its first participant on 27^th^ March 2026. Recruitment is ongoing with a planned recruitment period of 12 months, estimated to complete enrolment by 9th February 2027. Participants will be recruited from specialist PDN clinics, and their aligned primary care and podiatry services. Recruitment will be supported through digital promotion, including social media, and via local patient groups and charities. All study investigations and interventions will take place in clinical research facilities at the two sites. Data collection is expected to complete by September 2027 with results expected to be shared by February 2028.

### Standard of care in both arms

HCL insulin therapy will be administered alongside standard care without requiring participants to stop their usual neuropathic pain medications. During the trial, minor adjustments to pain medication may occur at the clinician’s discretion to maintain safety and comfort, though further dose escalation is unlikely. All changes will be recorded and included in the analysis. Continuation of standard care is ethically and pragmatically justified, reflecting real-world practice, and facilitating recruitment as withholding standard neuropathic pain treatment would be unacceptable.

### Interventions

#### Control intervention period: CGM only (Dexcom G7).

In the control arm, participants will continue to use the insulin regimen on which they enter the study. As per NICE Quality Standard QS208, CGM is standard of care for pwT1D in the United Kingdom [21]. All participants will be provided with a Dexcom G7 continuous glucose monitoring (CGM) system. Standardisation of the CGM used enables comparison of glycaemic metrics between participants.

The Dexcom G7 is a CE-marked device that is worn on the back of the upper arm, requiring replacement every 10 days with a 30-minute warm up period [22]. Participants will download the Dexcom G7 app onto their smartphones to enable cloud-based data sharing. Participants will receive formal instruction as per the device manual on how to use the Dexcom G7. During control arm visits, a diabetes clinician will review participants, analyse their glucose data, and provide advice on optimising insulin treatment and glycaemic management. Regular pain medication will be continued throughout the study with changes to neuropathic pain medication avoided where possible. All medication changes will be documented.

#### HCL intervention period: HCL + CGM (t:slim X2 + Dexcom G7).

At the start of the HCL intervention period, participants will attend an in-person training visit for instruction of use of the Control-IQ and a Dexcom G7 CGM, based on manufacturer guidelines. The t:slim X2 is a tethered insulin pump licensed in the UK for use with quick acting insulins (Humalog, NovoRapid, Lyumjev, Admelog, and Trurapi) [23]. Control-IQ is an advanced HCL algorithm that uses predictive technology to automatically modulate insulin delivery. It reduces or suspends basal insulin to mitigate impending hypoglycaemia and increases basal insulin delivery and administers automated correction boluses to address impending hyperglycaemia. The system also includes temporary modes for sleep and exercise that adjust glycaemic targets, and allows for the creation of multiple insulin profiles to accommodate different situations, such as illness. Comprehensive education will be provided on sick-day management, including protocols for preventing diabetic ketoacidosis and instructions to switch to back-up insulin pens in the event of pump malfunction or infusion set failure.

The 12-week data collection period will commence after the training visit. All devices will be connected to the Tandem t:slim X2 mobile app to facilitate continuous cloud-based data upload. To ensure a safe transition to the new technology, a dedicated safety visit (Visit 3A) will be arranged shortly after the first scheduled infusion set change. At subsequent clinical visits, a diabetes clinician will review pump and CGM data, and provide advice to optimise pump settings. Concordance with hybrid closed loop treatment will be reviewed. The key therapeutic focus will be on improving glycaemic variability. To mitigate the risk of treatment-induced neuropathy of diabetes (TIND), a gradual reduction in average glucose levels will be implemented for participants with higher baseline HbA1c (>11.0%), by use of the pump in open loop mode for up to two weeks. A dedicated support number will be available for participants in all arms and sequences of the study. If ongoing treatment with HCL was deemed to be deleterious by the principal investigators, for example, due to worsening neuropathic pain, recurrent diabetic ketoacidosis, or any unforeseen recurrent or persistent issue, the trial participant would be returned to standard care.

#### Outcomes.

The primary outcome is the within-participant change in 7-day average 24-hour pain on an 11-point NRS from baseline to the end of each 12-week treatment period (sample pain diary in S2 File). A statistically significant reduction in the pain score will be considered to indicate superiority of the HCL treatment compared to standard care. This endpoint and measurement tool are considered the gold standard for clinical trials in PDN, aligning with the core domains of the IMMPACT consensus recommendations and NICE guidelines [18,24–26]. A 3-month endpoint is consistent with prior PDN studies, previously demonstrated to be a sufficient timeframe for clinical changes to be observed [27,28].

#### Secondary outcomes.

While the primary outcome addresses the core IMMPACT domain of pain intensity, secondary outcomes are included to capture the other recommended domains of physical and emotional functioning, as well as patient global impression of change (Table 2).

**Table 2 pone.0357573.t002:** Pre-specified secondary outcomes.

Pain-related outcomes
Proportion reaching 30% (moderate) and 50% (substantial) reduction in pain NRS
Change in area under the curve (AUC) for all daily NRS scores (12-week intervention period)
Changes in validated pain questionnaires: • Brief Pain Inventory (Modified Short Form) – BPI (MSF) • Neuropathic Pain Symptom Inventory (NPSI)
**Physical and emotional functioning**
Changes in validated questionnaires: • EQ-5D-5L • 36-Item Short Form Health Survey (SF-36) • Beck Depression Inventory (BDI) • Type 1 diabetes-specific distress (T1-DDS)
**Global impression of change**
Patient- and Clinician-rated Global Impression of Change (PGIC and CGIC)
**Glycaemic outcomes**
Key glycaemic metrics derived from CGM data, including time below range (TBR) <3.0 mmol/L, TBR 3–3.9 mmol/L, time in range (3.9–10 mmol/L), time in tight range (3.9–7.8 mmol/L), time above range >10–13.9 mmol/L, time above range >13.9 mmol/L, coefficient of variation (CV), standard deviation (SD), and Glucose Management Indicator (GMI)
Haemoglobin A1c (HbA1c)
**Safety outcomes**
The frequency of adverse and serious adverse events

NRS – Numerical Rating Scale. Time below range (TBR).

#### Exploratory endpoints.

Neurophysiological assessments will be performed to further understand the underlying mechanisms of painful diabetic neuropathy and the impact of glycaemic variability on these parameters. Sleep parameters and physical activity will be explored as an objective proxy of pain evolution and management. Validated hypoglycaemia questionnaires (HypoA-Q and Hypoglycaemia Confidence Scale (HCS)) will be completed at baseline and at the end of each treatment period to explore the relationship between hypoglycaemia and PDN.

#### Participant timeline and data collection.

A summary of key activities for study participants at each visit is summarised in Table 1. As per this schedule, some visits can be conducted remotely. Prior to participation, prospective participants will be provided with the participant information sheet and given the opportunity to ask questions (S3 File). Written informed consent will be obtained by the PI or delegate (S4 File). Re-consent will be obtained for any protocol amendments. 70% completion rate of pain and sleep diaries, and CGM data from the 4-week screening period will be required to be eligible for randomisation.

A delay of three months from end of the four-week baseline data collection to start of the HCL twelve-week intervention period is permitted to allow scheduling of group starts. Three visits are scheduled during each 12-week intervention period to facilitate titration of treatment. Participants will continue to complete daily pain and sleep diaries until the end of the study. At the conclusion of each treatment arm, participants will attend a final visit for comprehensive data collection, including validated questionnaires (as listed in the secondary outcomes), a blood test for haemoglobin A1c, and neurophysiological assessments.

Changes in level of participation within the trial are categorised in the following ways – no trial intervention, no trial related follow-up, and no further data collection – depending on the participant’s wishes. Where the participant consents, the participant will continue to attend the original schedule of assessments. Where they consent to data collection but do not wish to attend trial visits, where possible, data will be collected at standard clinic visits.

#### Randomisation.

Participants will be randomised at the level of the individual in a 1:1 ratio to either Treatment Sequence A (HCL + CGM followed by CGM only) or Treatment Sequence B (CGM only followed by HCL + CGM) using a secure online randomisation programme. The randomisation will use the Pocock-Simon minimisation algorithm to ensure balance in the treatment allocation taking into account centre, age (18–39, 40–59, 60+) and gender at birth [29].

#### Blinding (masking).

Given the nature of the HCL intervention and the use of a visible device, it is not possible to blind participants to their assigned treatment arm. To mitigate potential bias from research staff, pain surveys are completed solely by the participants, with other secondary outcome assessments such as neurophysiological assessments and haemoglobin A1c yielding objective numerical data, which are not subject to assessor bias.

#### Distress protocol.

Given that some secondary outcome questionnaires assess sensitive topics such as depression and quality of life, there is a potential for participants to experience psychological distress. To mitigate this risk, a formal distress protocol is in place (S5 File). This includes providing immediate support from the trial clinician and a pre-established pathway for onward referral to a specialist mental health team if necessary.

#### Neurophysiological tests.

Four objective point-of-care neurophysiological assessments will be completed at baseline and at the end of each treatment period. The CE- and FDA-approved Sudoscan device (Impeto Medical ltd, Issy-les-Moulineaux, France) will be used to assess small-fibre neuropathy, based on sudomotor function. The test is a rapid and reproducible non-invasive assessment [30]. Participants place their hands and bare feet on electrode plates for 3 minutes. A low-voltage current (<4V) is applied to stimulate small fibres innervating sweat glands, and based on the electrochemical reaction between sweat chloride and stainless-steel electrodes, the resultant electrochemical skin conductance (ESC) is measured [31]. As per previous data, an ESC of <70 µS for Caucasian individuals and <60µS for Asian and African American individuals is considered diagnostic of DPN, whereas an ESC above these thresholds is considered normal [32].

The CE- and FDA-approved DPN-check (NeuroMetrix Inc, MA, USA), a handheld device with stimulating probes at one end and a biosensor at the other will be used to assess for large-fibre neuropathy [30,31]. The sural sensory nerve conduction velocity (SNCV;/m/s) and amplitude (sural nerve action potential (SNAP)) will be measured in both ankles, taking approximately 2 minutes. The device has an in-built infrared thermometer to measure skin temperature near the ankle, with subsequent SNCV readings normalised for skin temperature. DPN is associated with low SNAP and SNCV. The proprietary thresholds cut-offs for diagnosis of DPN using the DPN-Check are a SNAP ≤ 4 µV and/or SNCV ≤ 40 m/s in at least one leg. The DPN-Check’s software also provides an objective classification of neuropathy severity based on the measured SNCV and SNAP values, categorising the findings into four stages: 0 (Normal), 1 (Mild DPN), 2 (Moderate DPN), and 3 (Severe DPN).

Vibration perception thresholds will be examined using multifrequency vibrometry via the VibroSense Meter II device (VibroSense Dynamics, Malmo, Sweden). The VibroSense Meter II tests vibration sensation at 4, 8, 16, 32, 64, 125 and 250 Hz at the right metatarsal head [33]. The examination is fully automated, with the vibration applied via a probe and the participant pressing down on a response button if they perceive vibration. Prior studies have demonstrated associations between deficits in vibration sensation and a higher risk of developing diabetic foot ulcers, gait or balance problems or weakness of the feet [34].

Autonomic function tests will be conducted with the Vagus Device (Medicus Engineering, Aarhus, Denmark), a handheld device, validated to diagnose autonomic neuropathy via two-electrode ECG recordings [35]. Assessment will comprise of two main components: time-domain and frequency-domain parameters from 5-minute resting heart rate variability; and four cardiac autonomic reflex tests (CARTs). The four standardised CARTs performed will be the expiration: inspiration (E:I) heart rate ratio during deep breathing, the heart rate response to a valsalva manoeuvre at 40 mmHg via a disposable mouthpiece, and both the heart rate and blood pressure response to standing. Results will be compared to published age- and sex-matched normative thresholds, with results below the 5^th^ percentile deemed abnormal [35].

#### Activity and sleep tracking.

Participants will be asked to use a Withings’ sleep tracker mat (Issy-les-Moulineaux, France) and an activity monitor watch during the study period. Sleep parameters collected will include total sleep time, sleep interruption, the apnoea-hypopnea index (AHI – a measure of sleep apnoea), nighttime heart rate and heart rate variability. Physical activity measures include active minutes, steps and skin temperature. These parameters will be used as exploratory objective proxy measures of pain evolution and management.

#### Sample size justification.

To detect a minimally important difference of 0.75 NRS points (between-patient SD of 2, within-participant SD = 1.44) with 90% power and two-sided α = 0.05, a crossover/pairwise comparison requires 39 evaluable participants. Allowing for 20% dropout during the eligibility screening period, we will recruit up to 49 participants. The 0.75-point NRS difference reflects a 15% reduction from a conservative baseline NRS of 5, consistent with IMMPACT guidelines which define a 15% between-group difference as clinically meaningful [18]. Calculations use the within-individual SD appropriate for crossover designs and therefore are conservative for detecting a true within-participant treatment effect. Using a lower baseline than typically seen in NeuP trials ensures the study is robustly powered, even in patients with milder pain (effect size 0.52). Our estimated dropout rates are conservative and allow for an increased dropout rate compared to previous HCL trials [14,16].

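### The 39 participants and effect size 0.52 need 1.44 to be the SD of the paired difference; as the within-participant SD it is labelled, it gives about 61% power at 39, not 90%

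*Protocol article*

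**What the plan says.** All of the planning figures stand in one paragraph of the protocol article, Sample size justification. The calculation is set up "To detect a minimally important difference of 0.75 NRS points (between-patient SD of 2, within-participant SD = 1.44) with 90% power", with a two-sided α of 0.05. The section derives the 0.75 as 15% of a baseline NRS of 5. From these inputs it concludes that a crossover or pairwise comparison needs 39 evaluable participants, raised to at most 49 recruited for 20% loss during screening.

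The label on the SD is then repeated as a justification: "Calculations use the within-individual SD appropriate for crossover designs and therefore are conservative for detecting a true within-participant treatment effect". The section also gives a standardised effect, saying that the study is robustly powered "even in patients with milder pain (effect size 0.52".

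Study setting and recruitment adds that 40 participants are to be randomised. Nowhere does the article call 1.44 the SD of the difference between the two treatment periods.

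**The concern.** In a two-period crossover the treatment effect is estimated from each participant's difference between two period scores. The within-participant SD is conventionally the SD of one score around that participant's own mean, and the SD of a difference of two such scores is √2 times larger. The section sets its within-participant SD beside a between-patient SD, which is how the two variance components of a crossover are usually presented. The result printed, however, is the one obtained by entering 1.44 as the SD of the difference, without the √2.

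The printed label and the printed power therefore cannot both be right. The stake is the claim that justifies the sample size. If the label is correct, a true 0.75-point benefit would be missed in about 4 of 10 such trials, and a null result read against a stated 90% power would look like stronger evidence of no worthwhile benefit than it is.

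**Working it through.** **Inputs**, from Sample size justification unless noted: difference δ = 0.75; SD = 1.44; two-sided α = 0.05 (z = 1.960); power 90% (z = 1.2816); evaluable n = 39; 40 randomised (Study setting and recruitment).

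**1. Reproducing the plan's figures.** For a paired comparison, n = (z₀.₉₇₅ + z₀.₉₀)² × SD_d² / δ², where SD_d is the SD of the paired difference.
- With SD_d = 1.44: 10.507 × 2.0736 / 0.5625 = 38.7, rounded up to 39. This matches.
- Effect size: 0.75 / 1.44 = 0.52. This matches.
- Inflation: 39 / 0.80 = 48.75, rounded up to 49. This matches.

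All three figures agree with one another when 1.44 is SD_d.

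**2. The same inputs with 1.44 as labelled.** If 1.44 is the within-participant SD of a single period score, SD_d = √2 × 1.44 = 2.036.
- Effect size: 0.75 / 2.036 = 0.37, not 0.52.
- n for 90% power: 10.507 × 4.147 / 0.5625 = 77.5, so 78 (normal); 80 by the noncentral t.
- Power at 39, normal: 0.75 × √39 / 2.036 = 2.300, and Φ(2.300 − 1.960) = 63%.
- Power at 39, noncentral t: 61% (with 37 or 38 degrees of freedom).
- Power at the 40 randomised, noncentral t: 62%.
- Difference detectable with 90% power at 39: 3.2416 × 2.036 / √39 = 1.06 (normal), or 1.09 by the t with 37 degrees of freedom. As a share of baseline 5, these are 21% and 22%, against the 15% planned for.

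**3. Do other conventions rescue 39 under the label?** With SD_d = 2.036, a one-sided 5% test at 90% power needs 64, and a two-sided test at 80% power needs 58. Neither gives 39.

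**4. If 1.44 is the SD of the paired difference.** Power at 39 is 90.2% by the normal approximation and about 89% by the t; at 40 it is about 89% by the t. The stated 90% then holds to within the choice of approximation.

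**5. The claim of conservatism.** If 1.44 is a single-score SD, using it as the SD of a difference overstates power. If 1.44 is the SD of the difference, using it is simply correct. Neither reading makes the calculation conservative.

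**The case against.** The best answer is that the article uses within-participant to describe the contrast itself. The last paragraph of the Introduction calls the primary outcome a within-participant difference, and Sample size justification speaks of a pairwise comparison and a within-participant treatment effect. In that vocabulary the within-participant SD could be shorthand for the SD of the within-participant difference. On that reading 39, 0.52 and 49 are all consistent, and the fault is a loose label. This stands as a possible reading, and it is why 61% cannot be asserted as the trial's power. It does not remove the point. The section sets 1.44 against a between-patient SD and then describes it as the within-individual SD suited to crossovers, so a reader who takes the words in their usual sense gets a different sample size.

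Three stronger inferences are tempting and are not supported:

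- **That the trial is underpowered and must grow to 78 or 80.** This requires knowing that 1.44 is a single-score SD, which the document does not establish. Likewise, 38.7 is also the per-sequence number when 1.44 is a single-score SD, so a reader might suspect that a per-sequence figure was taken as the total. Nothing in the text shows that.
- **That 39 is wrong even when 1.44 is the SD of the difference, because the t gives 41.** That is a choice of approximation, and the power at 39 to 40 is about 89%.
- **That a particular between-period correlation is implied and should be declared.** With SD_d = 1.44 it is 1 − 1.44²/(2 × 2²) = 0.74 if 2 is the total SD of a score, but 4/(4 + 1.0368) = 0.79 if 2 is a pure between-patient component. The article does not say which, and such detail is commonly left to the full protocol.

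**Conclusion.** The point holds as an inconsistency between a printed input and a printed result. With the SD as labelled, power for 0.75 NRS at 39 evaluable participants is about 61% (t) to 63% (normal), and the trial has 90% power only for a difference of about 1.1 NRS. If the label is wrong and 1.44 is the SD of the paired difference, the sample size is sound and only the wording needs correcting. The sentence calling the calculation conservative does not follow in either case.

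The figures assume complete pairs, a simple paired analysis, equal variance in the two periods and the article's own 0.75 target. The mixed model's covariates do not alter the √2 relation between a single-score SD and the SD of a difference of two such scores.

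**What to change.** Check the source of 1.44 and state in Sample size justification which SD it is.

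- **If it is the single-measurement within-participant SD:** keep the label. Restate power at 39 for 0.75 NRS as about 61%, or restate the difference detectable with 90% power as about 1.1 NRS (21–22% of baseline 5). Correct the effect size from 0.52 to 0.37.
- **If it is the SD of the HCL-minus-control paired difference:** relabel it as such in both places. The 39 and 0.52 then stand on the normal approximation (about 89% power by the t at 39 to 40).
- **In either case:** delete the clause that calls the calculation conservative because it uses the within-individual SD.

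The cost is one reworded paragraph and, in the first case, a less favourable power statement. No correlation value needs to be added, and this correction does not call for more enrolment.
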